#

# ABSTRACT

**Background:** In Kenya, 1.4-1.6 million people are living with HIV, with an adult prevalence of 6.3%. Nyanza, one of the eight provinces, has the highest prevalence, at 13.9%. Within Nyanza, HIV prevalence in the districts occupied by the Luo - the dominant ethnic community in the province and third nationally – was 20.2% in 2008/09 (17.1% in men and 22.8% in women). Several drivers of the rapid spread of HIV in the province have been identified as, among others, lack of male circumcision. A large number of observational studies and three randomized controlled trials concurred in their findings, that voluntary medical male circumcision (VMMC) reduces men’s risk of acquiring HIV by about 60%. Following the publications of these results and subsequent endorsement by the World Health Organization and UNAIDS, Kenya rolled out VMMC services from October 2008. By June 2013, our organization had performed 241,145 circumcision procedures. However, uptake of services by older men (aged ≥25 years) who engage in behaviors that put them at higher risk of acquiring HIV has been low, at about 30%. We propose to evaluate the impact of two interventions (Inter-Personal Communication [IPC] and Dedicated Service Outlets [DSOs]) in recruiting men aged 25-39 years for VMMC services.

**Aims**: i) assess the rate of uptake of VMMC services among four categories of men: those exposed IPC, those exposed to DSO, those exposed to both IPC and DSO combined, and those receiving no intervention; ii) determine, through unlinked testing of blood from bleeding vessels from surgical wound, the proportion of men with unknown HIV status; and iii) determine the cost of providing VMMC among each of the three interventions vs. no intervention.

**Methods:** We will employ cluster-randomized controlled design. Through elimination by factors such as proximity to circumcising communities, multi-ethnic urban populations, and geographical proximity to each other, 45 administration Locations in Nyanza Province have been selected and randomized into IPC implemented alone, DSO implemented alone, IPC and DSO implemented together and control. Under IPC, we will develop a Toolkit for Addressing Barriers and Facilitators to VMMC with messages that address barriers to and reinforce facilitators of VMMC, and engage behavioral counselors to deliver intervention massages that are custom-made to address participants’ specific issues; Under DSO, selected facilities, days and hours will be set aside to serve only men aged ≥25 years; these sites will be served by older, male providers only; Under Combined IPC and DSO, the effect of both interventions implemented together will be examined; and in the Control locations, no intervention will be implemented. Altogether, 4,932 men aged 25-39 years are expected to take up VMMC during the study period, which will take up to nine months.

For aim 2, we will collect blood samples from bleeding vessels of an estimated 700 men whose HIV status is unknown, and perform unlinked test for HIV at the KEMRI/CDC HIV Laboratory in Kisumu. For aim 3, we propose to extract from our procurement, stores and accounts records expenditures for demand creation and service delivery.

To augment this study, we will nest a sub-study (sub-study 4) in all the 45 study Locations and enroll approximately 720 men who are in stable sexual relationships, together with their partners, for post circumcision follow up visits to monitor the impact of involving female partners on time to resumption of sex post-surgery.

# LIST OF ACRONYMS / ABBREVIATIONS

| Ab | Antibody |
| --- | --- |
| Ag | Antigen |
| CDC | Centers for Disease Control and Prevention |
| CEAC | Cost-Effectiveness Acceptability Curve |
| CHW | Community Health Worker |
| CI | Confidence Interval |
| CITI | Collaborative Institutional Training Initiative |
| CO | Clinical Officer |
| DALY | Disability Adjusted Life Years |
| DBS | Dried Blood Spot |
| DMPPT | Decision-Makers’ Program Planning Tool |
| DoD | Department of Defense |
| DSO | Dedicated Service Outlet |
| ED | Emergency Department |
| EDTA | Ethylenediaminetetraacetic Acid |
| ERC | Ethics Review Committee |
| FGD | Focus Group Discussion |
| GCP | Good Clinical Practices |
| GEE | Generalized Estimating Equations |
| HDSS | Health and Demographic Surveillance System |
| HIV | Human Immunodeficiency Virus |
| HIV-R Lab | HIV-Reference Laboratory |
| HR | Hazard ratio |
| ICC | Intra-cluster Correlation Coefficient |
| ICERs | Incremental Cost-Effectiveness Ratios |
| IDI | In-Depth Interview |
| IPC | Inter-Personal Communication |
| IPO | Infection Prevention Officer |
| IRB | Institutional Review Board |
| IRDO | Impact Research and Development Organization |
| KEMRI | Kenya Medical Research Institute |
| MC | Male Circumcision |
| MOH | Ministry of Health |
| NO | Nursing Officer |
| OR | Odds ratio |
| PEPFAR | United States President’s Emergency Plan for AIDS Relief |
| PI | Principal Investigator |
| PIN | Participant Identification Number |
| RA | Research Assistant |
| RR | Risk ratio |
| SOP | Standard Operating Procedure |
| SPSS | Statistical Package for Social Science |
| STATA | Data Analysis and Statistical Software developed by STATA Corp. Tx |
| STI | Sexually Transmitted Infection |
| UNAIDS | The Joint United Nations Programme on HIV/AIDS |
| USAID | United States Agency for International Development |
| VMMC | Voluntary Medical Male Circumcision |
| WHO | World Health Organization |

# BACKGROUND AND SIGNIFICANCE

Results of three randomized controlled trials in South Africa, Kenya and Uganda have confirmed beyond reasonable doubt that voluntary medical male circumcision (VMMC) is safe and reduces the risk of HIV acquisition in heterosexual men by approximately 60%.^[[1]](#endnote-1),^^[[2]](#endnote-2),^^[[3]](#endnote-3)^ These results supported findings from previous observational studies which also indicated that VMMC significantly reduces the odds of acquiring HIV by men.^[[4]](#endnote-4),^^[[5]](#endnote-5)^ A summary of prospective studies that enrolled HIV negative participants, followed them up and monitored the rate of new HIV infections, reported that male circumcision reduced the risk of acquiring HIV by 58% in the general population and by 71% among high risk groups, such as patients in sexually transmitted infection (STI) clinics and partners of female sex workers.^4^

The Government of Kenya began providing VMMC services in October 2008, with support from donor-funded implementing partners. IRDO is one of the VMMC implementing partners and a registered Kenyan non-governmental organization whose mission is to design, implement and evaluate public health research and programs in Kenya. Of the approximately 300,000^[[6]](#endnote-6)^ circumcisions done in Nyanza Province to date, only about 12% (our sites are at 16%) of clients are aged above 25 years, yet this is the age bracket that if circumcised would translate into an immediate impact on HIV incidence.^[[7]](#endnote-7)^ We propose to implement and evaluate the impact of two interventions – Interpersonal Communications (IPC) and Dedicated Service Outlets (DSO) – independently and jointly, on demand for VMMC by men age 25-39 years in Nyanza Province.

**Why target older men?** A meta-analysis^[[8]](#endnote-8)^ and modeling studies^7^ on male circumcision (MC) suggest that circumcising older, more sexually active men within a short period of time would have a bigger and faster population-level impact in reducing incident HIV. Hankins et al^7^ propose that since HIV incidence is highest among 25-34 year old men, circumcising men in this age bracket has the biggest benefit, whereas circumcising those aged 15-24 and 35-49 years has modest impact. Circumcising men 50+ years has little effect on HIV incidence. Thus, targeting the right age and speeding up coverage are key to making an impact on HIV incidence.

Although Kenya has set the pace of VMMC in Africa by circumcising about 500,000 men in the past 4 years,^[[9]](#endnote-9)^ the country has performed rather poorly in getting older men ≥25 to take up VMMC services. The difficulty in getting older men take up VMMC services is not unique to programs; in two recently concluded operations research in Nyanza, ^[[10]](#endnote-10),^ ^[[11]](#endnote-11)^ the median age of the 4,363 study participants was 20 and 21 years. While Kenya anticipates circumcising 860,000 men aged 15-49 years by 2013/14,^[[12]](#endnote-12),^^[[13]](#endnote-13)^  it is clear that getting older men remains a challenge. New strategies to make VMMC appeal to older men must therefore be conceived, implemented and evaluated. We intend to evaluate the impact of inter-personal communication and dedicated VMMC service outlets on uptake from an average of 30% to 40%.

While the increase from 30% to 40% may seem modest, the high risk of HIV associated with being uncircumcised in this area means that doubling MC could have a significant public health impact in terms of the number of HIV infections averted. Most males getting VMMC in Kenya have a median age of 17 years. In contrast, the uptake of VMMC by the older males remains low, being about 30% (unpublished data from a demographic surveillance survey in one of the districts in Nyanza Province) while they are more likely than younger men to acquire HIV. Modeling studies by Nagelkerke, 2008^[[14]](#endnote-14)^; Hankins 2009^7^; Njeuhmeli, 2011^[[15]](#endnote-15)^ have demonstrated a strong impact of increasing VMMC coverage in the long-term on the number of HIV infections averted, especially in regions with generalized HIV epidemics. They have shown that increasing uptake of male circumcision among adults (15 – 49 years) is associated with a simultaneous increase in the cumulative number of new infections averted. For example, in Nyanza province, it has been estimated that by performing 380,000 VMMCs between 2011 – 2015, about 100,000 HIV infections would be averted, while 570,000 VMMCs performed between 2011 and 2015 would avert 700,000 HIV infections. This implies that even a modest change in the additional number of VMMCs attained could result into a considerable increase in the number of HIV infections averted.

**Why interpersonal communication (IPC)?** IPC is a strategy that involves communication between/among a few people who are in close proximity and have a shared interest. It is a one-on-one or small group communication to discuss, educate, sensitize, influence, persuade, reason with peers, friends, family, workmates, and so on. This is done with a purpose of winning them for or against an idea or action. A large body of literature,^10,^^[[16]](#endnote-16),^^[[17]](#endnote-17),^^[[18]](#endnote-18),^^[[19]](#endnote-19),^^[[20]](#endnote-20),^^[[21]](#endnote-21),^^[[22]](#endnote-22)^ indicates that key barriers to VMMC among men in Nyanza include pain, fear of complications, concern over how to feed self and family during the healing period, and perception that the penis shrinks or sexual libido and/or performance diminishes after surgery. Other barriers include VMMC being viewed as against culture or religion, the recommended period of sexual abstinence perceived as being too long, unease with lining up for services with young people, and concerns over being circumcised by young and/or female providers. However, circumcision being a component of some religions could also be a reason for some men seeking circumcision. These studies also reported that most of those who take up VMMC have been influenced by peers, those who have gone through circumcision, female sexual partners, parents, older brothers, community elders, political and religious leaders, and school/college instructors. Three of the studies^16-18^ point to strong perception that VMMC is intended for younger men <21 years. The perception is that older men are in stable relationships hence insulated from HIV. This indicates that people still have personal questions and concerns that they want addressed before making a decision for VMMC. This calls for settings tailored to favor open discussion on barriers to service uptake. We intend to engage “influencers” of decisions around VMMC, such as satisfied clients, female partners, community leaders, community health workers, and older siblings. We will build their capacity to recruit older men through open, clear, concise and repetitive dialogue in the comfort of their homes.

**Why Dedicated Service Outlets (DSOs)?** There is growing anecdotal reports from implementing partners in Kenya that one of the key barriers older men cite for not taking up VMMC services is that they are uncomfortable being made to queue with young boys for fear of being labeled promiscuous given circumcision has largely been marketed as a strategy for preventing HIV and STIs. Similar reservations have also been expressed in a study in Tanzania,^[[23]](#endnote-23)^ where male respondents pointed out that VMMC services often do not take into account social status of potential care-seekers, specifically age and gender status. For example, there were concerns that older men are circumcised by young women, and sometimes wait in line with children and youth. Additionally, young men reported feeling ashamed to be served by women, to expose their nudity, be touched, and so on; they also fear sexual arousal if service providers are young female.

In response to the concern over age-mixing and female providers, we intend to set up special clinics to serve the older population (25+ years) that are friendly and with flexible working days and hours. In these clinics, we will engage mature, male service providers only, who are within/close to the same age bracket as the participants. If shared with other services, the designated clinics will strive to ensure discretion and privacy to the clientele. Where designated clinics are not feasible, we will set aside days for older men, in addition to providing services to older men over the weekends, in the evenings and during public holidays.

# STUDY AIMS AND JUSTIFICATION

***Aim 1: Assess the rate of uptake of VMMC services by men aged 25-39 years exposed to Inter-Personal Communication (IPC) vs. Designated (older men only) Service Outlets (DSO) vs. IPC and DSO interventions combined vs. no intervention.***

Justification: Since Kenya launched VMMC in November 2008, IRDO has circumcised 241,145 men as at June 2013, aggregated by age as follows: 88% under 24 years, 12% 25-39 years, and 2% ≥40 years. IRDO’s performance is relatively better than the provincial rate, which stands at under 10%, a clear demonstration that creative strategies to create demand for VMMC among older men are urgently needed if the country is to experience the immediate benefit of VMMC on HIV incidence. We will register all participants coming for VMMC services at our sites and document their assigned arm and date of circumcision. At enrollment, we will capture the details of each participant enrolled in the study and enter them into a Participants Master Log (Appendix 14), which comprise of all enrolled participants at baseline. The details will include: participant’s 3 names, national ID number, age, location, village, telephone number (of the participant or close friend) and date of enrollment. At endline, we will extract program data on MC uptake among clients aged 25-39 years in non-study VMMC health facilities and triangulate with those registered in the Participants Master Log as having been circumcised. The purpose of this comparision is to capture study participants who may have been circumcised in non-study health facilities (further discussion is on page 41).

***Aim 2: Determine through testing of unlinked de-identified blood from bleeding vessels from surgical wound, the proportion of men whose HIV status is unknown who are HIV infected (Sub-study 1).***

Justification: HIV testing and counseling is one of the components of comprehensive VMMC services recommended by the World Health Organization and the Government of Kenya. However, our program data indicate that testing currently stands at about 74%, and questions arise if those who decline testing could have higher prevalence than those accepting to be tested. While VMMC is not denied to those who test positive for non-HIV prevention reasons, counseling messages for those known to be HIV infected differ from those who are HIV-negative. It is therefore important to compare HIV prevalence among those who opt to know their HIV status and those with unknown status to provide information that will inform counseling messaging among the latter group.

We will perform the testing of blood from bleeding vessels of those of unknown HIV status. The samples will be sent for testing at the KEMRI/CDC Laboratory in Kisumu.

***Aim 3: Determine the cost of providing VMMC among the three interventions relative to each other and to no intervention.***

Justification: Costing of new interventions help in making policy decisions regarding their viability for adoption. Our programs data have indicated that with sufficient demand for services, which we hope to create among older men through the proposed interventions, the cost of VMMC are expected to go down markedly. We will extract uptake data from procurement, stores and accounting records in terms of numbers of MCs done, and identify all expenses that went into each intervention and calculate the unit cost of each demand creation intervention.

## RESEARCH STRATEGY/APPROACH

## **STUDY DESIGN**

We propose to conduct a cluster randomized-controlled trial, with Locations forming the unit of randomization. Locations are the third smallest administrative units in Kenya after Province, District and Division and before Sub-Location and Village. Within the selected Locations, we shall randomly select approximately 16% of the villages which will be sufficient to generate the required sample size (see Tables 4 & 5 below). We shall visit 209 villages, as explained below (Table 5).

**Sample size Determination**

Sample size for detecting the impact of the interventions on VMMC uptake

Unpublished data from an on-going demand creation study and an HIV community based study show an average of 30% circumcision prevalence in the target group (25-39 years); a corresponding refusal rate of 15% and loss to follow-up of 15%. Using an average MC uptake of 30%, an intra-cluster correlation coefficient (ICC) of 0.005, and a design effect of 2.5 in sample size formula for cluster studies, we estimated that in order to be able demonstrate at least a 33.3 % increase in the rate of VMMC among young adult men in intervention arms when compared to those in control arm with 80% statistical power, and Bonferroni adjusted two-sided $\alpha=(\frac{0.05}{3})=0.017$ following the implementation of study interventions , we will need a sample size of 4,932 men reached with the intervention.

The graph below (*Figure 1)* shows that an effect size equal to 33.3% increase in MC from 30% to 40% will require about 1233 participants per study arm (total 4932), while an effect size equal to 50% increase in VMMC from 30% to 45% will require 573 participants per study arm (total 2292).

Adjusting for refusal rate of 15% and a loss to follow up of 15%, suggests contacting 1603 per study arm resulting in a total of 6412 uncircumcised men aged 25-39 years.

Fig.1 shows a range of sample size requirements for detecting various percentage increases (effect sizes) in VMMC uptake due to the interventions assuming causal effect, and for an 80% power, a 1.7% significance level and a two sided test.

[figure not shown]

Figure 1: Sample Size Vs Percentage Increase in MC Uptake

Selection of Clusters (Locations):

The CONSORT (consolidated standards of reporting trials) extension for cluster randomized trials which provide guidelines on quality of reporting and study methodology of cluster randomized trials recommends a minimum of 4 clusters per arm.^[[24]](#endnote-24)^ Since greater statistical power and precision are obtained by sampling more clusters than sampling a higher number of study participants per cluster, we sought to sample as many eligible locations as was feasible as long as they did not share boundaries. Out of the 164 Locations across nine study districts^[[25]](#footnote-1)^ in Nyanza Province (Figure 1), we will systematically selected 45 Locations. Each Location is expected to have about 700 men in the 25-39 age bracket^[[26]](#endnote-25)^ of whom about 500 are likely to be uncircumcised (based on circumcision program data and demographic surveillance survey which is about 30%).

The selection and randomization of participating Locations was accomplished by a team of three (KA, EO and [name] – a former study coordinator). The four steps below describe the process of selecting and randomizing the 45 Locations where the study will be conducted:

1. Sampling frame (total number of Locations in IRDO districts): According to the 2009 Kenya Population Census Report, Nyanza Province has 14 districts and 233 **administrative Locations** inhabited by traditionally non-circumcising *Luo* ethnic community (i.e. where circumcision is not a cultural practice). IRDO currently provides VMMC services in 12 of the 14 districts, and 194 of the 233 Locations. Out of these, the study will be done in 11 districts. Another study is planned for the one remaining district under IRDO. We contracted a cartographer to generate a GIS map showing the 11 districts and 164 Locations where IRDO will conduct this study (Fig 2: Map 1).
2. Separating eligible from ineligible Locations: To ensure the populations in participating Locations are as homogenous as possible in terms of ethnicity (which defines circumcising and non-circumcising communities), we spread the map on a flat surface and systematically identified and excluded 37 Locations: 34 bordering traditionally circumcising communities in Kuria, Gucha, Central Kisii, Nandi, Vihiga, Butere-Mumias and Busia districts, and 3 within cosmopolitan Kisumu city where mixed ethnic communities live. In addition, we excluded 5 Locations in the islands due to poor access. Consequently, we remained with 122 eligible Locations to select from (Fig 2: Map 2).
3. Selecting participating Locations: Of the remaining 122 eligible Locations, we randomly selected the starting point and went through the process of systematically selecting each Location and excluding all the contiguous ones until we identified the maximum possible Locations that did not share a boundary. This exercise was done repeatedly by randomly selecting different Locations as the starting point and seeing how many Locations we ended up with. The goal was to select the highest number while ensuring none is proximal to each other. Based on these selection criteria, 45 was the maximum number of Locations that could be included in the study (Fig. 2: Map 3).
4. Random assignment of participating Locations: The names of the 45 Locations were compiled and submitted to the study Biostatisticians (FO & VS) for randomization.The names were entered into Stata V12 statistical package and a randomization schedule produced using the random-number generator. Using simple randomization to allocate clusters, roughly equal number of Locations (11-12 per arm) was allocated to each of the four study arms (Fig 2: Map 4).

A summary of the steps and the number of locations are shown in *Table 1* below while randomization and distribution of allocation to the study arms by districts are shown in Tables 2 and 3.

**Table 1:** Summary of Selected Study Locations

| **Total Locations in *Luo* Nyanza Province** | 233 |
| --- | --- |
| Locations where IRDO is providing VMMC services | 194 |
| Locations excluded because of an ongoing pilot demand creation study | 30 |
| Locations excluded because they border traditionally-circumcising communities | 34 |
| Locations excluded because of having a multi-ethnic population | 3 |
| Locations excluded because of poor accessibility (Islands) | 5 |
| Locations eligible for selection | 122 |
| Locations excluded because they are proximal to a previously selected Location | 77 |
| Number of Locations selected for the study | 45 |

**Table 2:** The number of Locations assigned to each study arm by district

|  | **Study Arm** | | | | **Total** |
| --- | --- | --- | --- | --- | --- |
| **District** | **Control** | **IPC** | **DSO** | **IPC+DSO** |  |
| Bondo | 1 | 1 | 1 | 1 | 4 |
| Homabay | 1 | 1 | 2 | 1 | 5 |
| Ndhiwa | 1 | 1 | 2 | 1 | 5 |
| Kisumu East | 1 | 0 | 2 | 1 | 4 |
| Kisumu West | 1 | 1 | 0 | 1 | 3 |
| Nyatike | 1 | 2 | 1 | 2 | 6 |
| Migori | 1 | 0 | 0 | 1 | 2 |
| Rarieda | 1 | 1 | 0 | 0 | 2 |
| Rongo | 0 | 1 | 0 | 2 | 3 |
| Siaya | 1 | 2 | 1 | 2 | 6 |
| Suba | 2 | 1 | 2 | 0 | 5 |
| Totals | 11 | 11 | 11 | 12 | 45 |

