At enrollment, participants will be given 3 months within which to go for circumcision, Participants can go whenever they want for VMMC, but our study will only capture their data if they go within 3 months. They will also be informed that a reminder of the expiry date for circumcision will be sent through text message to all participants one month before the expiry of the circumcision window period. The message will read: “***One month remaining. Take action for your health now***”. Participants will be informed at enrollment that they will be sent a text with the 3 words as a reminder that in case they have not gone for circumcision, they have 1 month remaining. This information has been captured in Written Informed Consent Form for Enrollment and Verification of Circumcision Status (Appendix 2A) as follows: **You have up to 3 months within which to go for circumcision. However, you are encouraged to go for circumcision as soon as possible; we recommend that it be within the next 3 months. Two months from now, you will be reminded through a text message to go for circumcision. The message will read: “*One month remaining.*** ***Take action for your health now*”.** The message is general and safe to receive even through a friend’s phone for those who do not own phones. A reminder is important because in an ongoing study on demand creation for VMMC in Kenya (funded by the Bill and Melinda Gates Foundation), preliminary results from the qualitative component reveal that participants who did not go for circumcision wished they were reminded because they simply forgot.

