**Estimated study participant accrual period**

Following a review of recruitment data from numerous studies of VMMC (IRDO program data) that we have previously conducted in several sites in the study area some of which have been selected for study implementation in this application, we estimate a conservative average study-wide combined accrual rate of 822 eligible men (25-39 years) per month across the 45 sites (18-19 men per Location per month).

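### The sample size takes the 30% prevalence of existing circumcision as control-arm uptake, so 80% power is not established for the endpoint, which is new circumcision among uncircumcised men

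*Protocol*

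**What the plan says.** Sample size Determination introduces the baseline figure as a prevalence: unpublished data "show an average of 30% circumcision prevalence in the target group (25-39 years". The next sentence relabels it as uptake and feeds it into the calculation: "Using an average MC uptake of 30%, an intra-cluster correlation coefficient (ICC) of 0.005, and a design effect of 2.5 in sample size formula". The result is that an "effect size equal to 33.3% increase in MC from 30% to 40% will require about 1233 participants per study arm (total 4932", at 80% power and a Bonferroni-adjusted two-sided alpha of 0.017. The men to be contacted (1,603 per arm, 6,412 in total) are counted as uncircumcised.

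A figure of about 30% also serves another purpose. Under Selection of Clusters each Location is expected to hold about 700 men aged 25-39, "of whom about 500 are likely to be uncircumcised (based on circumcision program data and demographic surveillance survey which is about 30" per cent. Table 4 makes the same reduction by district, for example 38 men per 100 households becoming 27 in Bondo.

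Participant Inclusion and Exclusion Criteria admits only uncircumcised men. Data Analysis, Aim 1, names VMMC uptake as the main outcome and assesses it as the proportion of uncircumcised men aged 25-39 who accept circumcision. Phase 3 says men may go at any time, "but our study will only capture their data if they go within 3 months".

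**The concern.** A prevalence among all men aged 25-39 stands in for the probability that an uncircumcised man is newly circumcised during the trial. The first counts circumcisions accumulated up to the date of a survey. The second starts at zero for every participant and runs over a short window. The two need not be close, and the protocol gives no argument that they are.

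About 30% is first used to take circumcised men out of the target population, and then 30% is assumed again as uptake among the men who remain.

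The stated power and detectable effect are what a reader will use to interpret a null comparison. If they are computed for a control proportion that is not the endpoint's, that interpretation has no basis. The text also leaves open whether the target is a ratio (33.3% more) or a difference (10 points). The two coincide at a control uptake of 30% and diverge sharply at lower values.

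**Working it through.** **1. Reproducing the plan's figure.** Inputs from Sample size Determination: p1 = 0.30, p2 = 0.40, alpha = 0.017 two-sided (z = 2.387), power 80% (z = 0.842), design effect 2.5.

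n0 = [z_a·√(2·p̄(1−p̄)) + z_b·√(p1(1−p1) + p2(1−p2))]² / (p2−p1)², with p̄ = 0.35, gives 472.8.

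Continuity correction: n = (n0/4)·[1 + √(1 + 4/(n0·|p2−p1|))]² = 492.6, rounded up to 493. Then 493 × 2.5 = 1,232.5, or 1,233 per arm, as stated. The second case, "50% increase in VMMC from 30% to 45% will require 573 participants per study arm (total 2292", also reproduces: 229 × 2.5 = 572.5, or 573. So 30% was used as the control-arm proportion, and the arithmetic is right for that input.

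**2. What the 30% is.** 700 × 0.70 = 490, close to the 500 uncircumcised men given per Location. In Table 4, 38 × 0.70 = 26.6 (shown as 27) and 32 × 0.70 = 22.4 (shown as 22). Both treat about 30% as men already circumcised. Those men are ineligible, so the proportion circumcised at enrolment is 0% in the analysed population.

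**3. What the endpoint's control proportion would be.** The document does not say, so it is an assumption here, shown from 2% to 30%. The low end corresponds to 30% coverage built up at a constant rate over 48 to 60 months: 1 − 0.7^(3/48) = 2.2% and 1 − 0.7^(3/60) = 1.8% per three months. The high end is the protocol's own figure.

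**4. Power at the planned size.** Effective n = 1,233/2.5 = 493.2 per arm; alpha = 0.05/3 (z = 2.394); no continuity correction.

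Power = Φ{[(p2−p1) − z_a·√(2p̄(1−p̄)/n)] / √([p1(1−p1) + p2(1−p2)]/n)}.

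Example, 10% v 13.33%: p̄ = 0.1167; null SE = √(0.2061/493.2) = 0.02044; alternative SE = √(0.2056/493.2) = 0.02042; power = Φ[(0.0333 − 2.394 × 0.02044)/0.02042] = Φ(−0.76) = 22%.

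| Assumed control uptake | Power, +33.3% relative | Power, +10 points | Contrast detectable with 80% power |
|---|---|---|---|
| 2% | 4% | over 99.9% | 2% v 6.0% |
| 5% | 10% | 99.8% | 5% v 10.5% |
| 10% | 22% | 98% | 10% v 17.0% |
| 20% | 53% | 89% | 20% v 28.8% |
| 30% | 82% | 82% | 30% v 39.8% |

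The last row gives 82% rather than 80% because the continuity correction is left out.

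**5. A third possible target.** If the aim is coverage among all men rising from 30% to 40%, the extra 10 points must come from the 70% who are uncircumcised: 0.10/0.70 = 14.3 points among the enrolled men. That is neither of the two readings in the table.

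**The case against.** The strongest reply is that the trial may be amply powered. Background and Significance gives the aim as moving uptake from an average of 30% to 40%, and Sample size Determination repeats those two figures, so a difference of 10 points is at least as natural a reading as a ratio of 1.33. On that reading a control uptake below 30% raises power. This stands. A reader might infer that the trial was underpowered and could not have detected an effect, but the document does not support that, because the result depends on which effect is meant.

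A reader might also try to fix the control rate from the section on the accrual period, which gives a "combined accrual rate of 822 eligible men (25-39 years) per month across the 45 sites". Dividing three months of that by the 43,172 uncircumcised men of Table 5 gives 3 × 822/43,172 = 5.7%. This fails. The section is about study accrual, and 4,932/822 is exactly 6 months, so 822 is consistent with the pace of enrolling the sample, not with background uptake.

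Further points have some force. The 2% is a community rate under a constant-hazard assumption, whereas enrolled controls receive a home visit, an interview, the information booklet and a text reminder, so 2% is an extreme and not an estimate. The three-month window is stated in Phase 3, but Data Analysis defines the main outcome without a window and adds an endline survey; a longer horizon would raise the control proportion. The two uses of 30% are attributed to differently described unpublished sources, so it cannot be confirmed that they are one estimate. None of this supplies an expected uptake among uncircumcised men.

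Data Analysis also plans to compare endline with baseline data, where prevalence would be the natural scale. That does not rescue the 30%, because both the main outcome and the sample size are defined in uncircumcised men.

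**Conclusion.** The point holds in this form: the control-arm input is the prevalence of existing circumcision, the endpoint is new circumcision among men who are all uncircumcised at entry, and no control uptake for that endpoint is given. The stated 80% power for 30% v 40% is therefore not established for the trial's main outcome.

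The size and direction depend on the target. Over an assumed control uptake of 2% to 20%, power is about 4% to 53% for the 33.3% relative increase and 89% to over 99.9% for 10 points; both are 82% at 30%. These figures rest on 1,233 analysed men per arm, the protocol's design effect of 2.5, alpha 0.05/3 and a normal approximation without continuity correction. The 2% to 30% range is an assumption.

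A reader might extend the point to the number of samples expected in the HIV sub-study. That is a separate matter: the yield there comes from applying 23.6% and 60% to all 4,932 men, and the 30% does not enter it.

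**What to change.** Rewrite the Sample size Determination paragraph on the analysed endpoint, in three steps:

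- Define the proportion as enrolled uncircumcised men newly circumcised by a stated outcome horizon, and use the same horizon in Phase 3 and Data Analysis.
- Declare the target effect as one of: a 33.3% relative increase; an increase of 10 percentage points; or coverage rising from 30% to 40%, which is about 14 points among uncircumcised men.
- Replace the single 80% figure with the table of power and detectable contrasts at 1,233 per arm over an assumed control uptake of 2% to 30%. Label that range as an assumption, and describe the 30% from the unpublished data as prevalence only.

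The cost is protocol wording and a stated power that varies with the assumption. Enrolment does not change.
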